### End of Study Visit

After admission to hospital or when pre-hospital care has ended, the physician will notify the site investigator or designee (SI) of any included patient. The SI will then take over responsibility for data collection.

The SI will debrief the physician at an appropriate time and will provide study information to the next of kin and access deferred consent, as described in chapter 8. The SI will gather and register necessary data in the case report form (CRF) and upload the ultrasound file to the secure data storage.

If adverse events occur, the SI will follow as per protocol.

## After End of Treatment (Follow-up)

We use a 30-day follow-up period and any adverse effects related to the procedure is likely to be found during this period. The follow-up is performed by the site investigator or designee. The SI will perform a chart review and a telephone interview, or face to face meeting if applicable, with the patient or the patients’ legal representative.

The SI will also perform the follow-up one year after randomisation and register the result in the CRF.

### Follow-up medical care

All patients will receive standard clinical care after randomisation or after the intervention is performed.

The patients included in the intervention group will eventually need removal of the REBOA introducer and catheter. In Norway this is performed by interventional cardiologist or interventional radiologist, depending on intra-hospital policies. This will be agreed upon with the project management, the site investigator and the relevant Head of Clinic before the study site can enter the study. Foreign study sites will provide the project management with documentation on how this will be handled before the study site can enter the study.

## Trial Discontinuation

The whole trial may be discontinued at the discretion of the sponsor in the event of any of the following:

- Occurrence of adverse events unknown to date in respect of their nature, severity and duration
- Medical or ethical reasons affecting the continued performance of the trial
- Difficulties in the recruitment of patients
- Changes in funding

If the interim analysis report significant group difference in primary endpoint, the study can be stopped. A recommendation to the sponsor to stop the study will only happen after a face to face meeting of the project management.

The study may be suspended or terminated by a site investigator at any time. The SI can only suspend or terminate the study at his/her study site.

The study may be suspended or terminated if serious safety issues are raised. This includes malfunction of equipment, indications of misuse of equipment or inappropriate performance skills in one or more of the physicians.

The data monitoring committee can recommend the sponsor to suspend or terminate the study if they find grave and unsolvable safety issues.

## Laboratory Tests

Several blood samples are commonly drawn from patients admitted after OHCA. We will register results from these samples, both to address possible differences between the groups, but also to assess a potential visceral hypoperfusion in the intervention group, as discussed in chapter 13.

There will be no biobank established and all laboratory test in this trial will be performed in accordance with laboratory standard procedures.

## Concomitant therapy

Concomitant therapy and medical interventions in the pre-hospital phase will be registered in the CRF.

No medication excludes participants from being included in this trial. Medications used by patients prior to inclusion in this trial, such as anticoagulants, will be recorded if information is available at the time of inclusion. All medications administered as part of the cardiopulmonary resuscitation is recorded in the CRF. Medications will be recorded as generic name, dose and route of administration.

Cardiopulmonary resuscitation may include both medications and techniques like thoracotomy or dual sequential defibrillation. These treatments will not differ in the two study groups. Concomitant therapy and medication between admission to hospital and evaluation after 30 days will not be registered.

# Data collection and processing

## Data handling

**Case Report Forms (CRFs)**

Data from each patient will be entered into an electronic database, a web-based case report form (webCRF3, <https://webcrf3.medisin.ntnu.no/>). This is developed and handled by the department KlinForsk, Clinical Research Unit, Central Norway. KlinForsk is authorised as data processors by the Norwegian Centre for Research Data. KlinForsk will set up necessary accounts to permit access to the CRF.

**Source Data**

Data are collected from

- Air ambulance journal the physician submits after an out-of-hospital cardiac arrest
- Ambulance journal
- Utstein pre-hospital cardiac arrest journal
- Data file from patient monitor used (in Norway this is most often Tempus Pro^TM^, RDT, United Kingdom or Corpuls3, GS, Germany). The monitor used may differ between study sites.
- Data file from cerebral oximetry system, e.g. ForeSight, Edwards Lifesciences Corp., USA. The system used may vary during the study.
- Checklist with registrations and inclusion criteria for the procedure (appendix 29.5).
- The site investigator will debrief each physician after the procedure, following a semi-structured interview template (appendix 29.6).
- The ultrasound images from the ultrasound machine used.
- The electronic patient journal, including laboratory tests.

**Storage of Study Documentation**

All data handling will follow strict security and privacy controls in compliance with Norwegian health and privacy laws. Electronic data gathered specifically for this trial (ultrasound images, copies of the monitor files) will be uploaded and stored in a private REBOARREST data space in HUNT Cloud, a part of HUNT data centre (<https://www.ntnu.edu/mh/huntcloud/about>). Access will be restricted to authorized users only on a need to know and need to do basis. Data will be protected in compliance with HUNT Cloud's ISO certificates for security and quality management (ISO 27001 and ISO 9001) as of today applicable to 161 security controls for which two-factor authentication is one.

Hard copies of patient documents, paper CRF’s or other printed document that may include identifiable information will be stored at a locked location at each study site or at the study coordinating centre, Rosten, Trondheim. Only the site investigator has access to this information. The Project Manager will have access to the information stored at the study coordinating centre.

Original trial documents (signed consent forms, notes from interviews with performing physicians, copies of patient journals, records of serious adverse events or other relevant correspondence) will be stored at the study sites or at the main research centre at Rosten, Trondheim, for five years to allow for inspection by relevant authorities.

When the data, either paper or electronic, are archived, the site investigators will maintain confidentiality of the data and prevent accidental destruction of documents. Paper and electronic data will be retained at least five years after the trial is finished.

## Data collection during study period

Data will be registered according to this schedule.

[figure not shown]

These data points will be registered:

| **All patients** - data reported after randomisation | |
| --- | --- |
| Age |  |
| Gender |  |
| Habitus | *Cachectic, Normal, Adipose* |
| Location of the incident | *Public outdoors, public indoors, private indoors* |
| All concomitant medication and dose used |  |
| Route of administration | *Intravenous, intraosseous* |
| All relevant times | *DD.MM.YYYY: hh:mm* |
| Time of dispatch |  |
| Time of arrival |  |
| Time of randomisation |  |
| Cardiac rhythm at randomisation and fluctuations in rhythm during resuscitation | *VF, VT, PEA, AS* |
| Suspected aetiology of arrest | *cardiac, respiratory, intoxication/poisoning, non-traumatic haemorrhage* |
| Number of defibrillations | *n* |
| Compression machine used | *yes/no* |
| Airway management (main method) | *Supraglottic airway, Endotracheal intubation* |
| ROSC more than 20 minutes | *yes/no* |
| Data file from monitor used |  |

| **Control group - additional data** | |
| --- | --- |
| End-tidal CO2 measures after randomisation and after ROSC | *kPa* |
| Other relevant times | *DD.MM.YYYY hh:mm* |
| Time of ROSC |  |
| Time of departure from scene |  |
| Time of admission to hospital |  |

| **REBOA group - additional data** | |
| --- | --- |
| Space to perform procedure | *Good/acceptable, Challenging, Impossible* |
| Visibility/light conditions | *Good/acceptable, Challenging, Impossible* |
| Temperature | *Good/acceptable, Challenging, Impossible* |
| Wind/rain conditions | *Good/acceptable, Challenging, Impossible* |
| Available resources on the scene that were used | *Bystanders, Another doctor, Ambulance, Fire brigade* |
| Ultrasound image obtaining | *Good/acceptable, Challenging, Impossible* |
| Data file from ultrasound machine |  |
| Cannulation site | *Left, Right* |
| Numbers of cannulation attempts | *n* |
| End-tidal measures | *kPa* |
| Before and after inflation of balloon, and after ROSC |  |
| Palpable pulse in left radial artery | *yes/no* |
| before balloon inflation |  |
| after balloon inflation |  |
| Other relevant times | *DD.MM.YYYY hh:mm* |
| Time of balloon occlusion |  |
| Time of ROSC and deflation of the balloon |  |
| Time of departure from scene |  |
| Time of admission to hospital |  |

| **Delivered to hospital - additional data** | |
| --- | --- |
| Blood gas from admission |  |
| pH |  |
| pCO2 | *kPa* |
| pO2 | *kPa* |
| SaO2 | *%* |
| Base Excess | *mmol/L* |
| HCO3 | *mmol/L* |
| s-Lactate | *mmol/L* |
| s-K | *mmol/L* |
| s-Na | *mmol/L* |
| s-Ca | *mmol/L* |
| Glucose | *mmol/L* |
| Blood sample analysis, up to 30 days, with time and date for samples | *DD.MM.YYY hh:mm* |
| White blood cells | *x10^3^/uL* |
| Blood platelets | *x10^3^/uL* |
| CRP | *mg/L* |
| Neuron Specific Enolase (NSE) after 48-72 h | *ug/L* |
| Troponins | *ng/L* |
| CK-MB and total-CK | *ug/L and U/L* |
| PT-INR |  |
| ASAT, ALAT | *U/L* |
| Bilirubin | *umol/L* |
| Albumin | *g/L* |
| Creatinine | *mmol/L* |
| Estimated GFR |  |
| Urine output, up to 30 days | *ml/day* |
| Complications related to REBOA equipment, with time and date for each complication | *yes/no, DD.MM.YYYY hh:mm* |
| Local haemorrhage requiring treatment |  |
| Lower limb ischemia |  |
| Infection requiring antibiotic treatment |  |
| Aortic dissection, rupture or injury |  |
| Femoral vessel dissection, rupture or injury |  |
| Surgical intervention/repair needed |  |
| Need for amputation  Other |  |
| Cardiac interventions  REBOA equipment used for in-hospital procedure | *PCI, IABP, IMPELLA, ECMO, other*  *Yes/no for each procedure* |
| Length of stay at intensive care unit during the 30-day period after randomisation | *number of days* |
| Length of stay in hospital during the 30-day period after randomisation | *number of days* |
| Length of invasive respiratory support during the 30-day period after randomisation | *number of days* |
| Length of renal replacement therapy dependency during the 30-day period after randomisation | *number of days* |
| Modified Rankin scale at day 30 | *0 to 6* |
| Survival one year after randomisation | *yes/no* |
| Results from radiologic exams first 30 days |  |
| Results from echocardiography first 30 days |  |
| Data from autopsy, if performed |  |

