## Secondary objective of the study

Secondary objectives of this trial are to describe the hemodynamic physiology of aortic occlusion during ACLS and a description of any adverse events and 30 days survival with good neurological status.

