## Exploratory endpoints

1. All-cause mortality one year after randomization
2. Difference in organ function, using the Acute Kidney Injury Network (AKIN) classification, liver function blood tests and others.
3. Incidence of all adverse events

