**Adverse event (AE)**

Any untoward medical occurrence, unintended disease or injury, or untoward clinical signs (including abnormal laboratory findings) in subjects, users or other persons, whether or not related to the investigational medical device (Figure 7).

Note 1: This definition includes events related to the investigational medical device or the comparator.

Note 2: This definition includes events related to the procedures involved.

Note 3: For users or other persons, this definition is restricted to events related to investigational medical devices.

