**Expected adverse events common to both treatments**

- Death
- Multi-organ failure
- Extremity ischemia
- Abdominal and/or pelvic ischemia that may/may not require surgical intervention
- Stroke (embolic or related to hypoperfusion)
- Paralysis
- Paraplegia, permanent or temporary
- Renal complications requiring renal replacement therapy

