## Period for recording adverse events

For each patient the standard period for collecting and recording AE will be from randomization and until admission to hospital.

For each patient the standard period for collecting and recording SAE will be from allocation and until the 30 day follow up visit. At the 30 day visit an assessment will be made where we specifically ask for all SAEs prespecified in this protocol. We will also assess discharge notes for other events that fulfil the SAE definition and that can be assessed by the study team.

For patients still admitted to hospitals at day 30, an effort will be made to secure access to main discharge note for assessment for any SAE that has occurred between day 30 and discharge.

Any information that comes to investigators attention for any included patient prior to the end of trial will be assessed according to this protocol.

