## Recording of adverse events

Patients in this trial are critically ill and are expected to need a prolonged hospital stay, often in intensive care unit and with several interventions. Both the standard care prior to arrival in hospital and during their stay have significant risks for adverse events. Expected serious adverse events will be recorded in the CRF, but not reported to the sponsor.

Adverse events occurring between allocation and the end of treatment phase by pre-hospital services will be fully recorded. Events occurring between end of treatment by pre-hospital services and day 30 will only be collected by checking hospital discharge note and paper CRF filled in by the SI after contact with the admitted hospital. The SI will assess the event for seriousness, causality, severity and expectedness before the event is registered in the CRF.

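### The in-hospital complication checklist records occurrence and REBOA attribution in one tick, so ascertainment is unequal between arms, mainly for non-serious access-site bleeding and infection

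*Protocol*

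**What the plan says.** Section 12.2 has one table for controls, one for the REBOA group, and then a shared table headed "Delivered to hospital - additional data". The shared table contains the item "Complications related to REBOA equipment, with time and date for each complication". Under it are yes/no entries for treated local haemorrhage, lower limb ischaemia, infection needing antibiotics, aortic injury, femoral vessel injury, surgical repair and amputation, plus an open entry.

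The rest of the protocol treats adverse events without regard to cause:

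- Section 14.1 defines an adverse event as an untoward occurrence "whether or not related to the investigational medical device".
- Section 6.5 sets the exploratory endpoint "Incidence of all adverse events".
- Section 6.2 makes "a description of any adverse events and 30 days survival with good neurological status" part of the secondary objective.
- Section 14.8 separates the ratings: "The SI will assess the event for seriousness, causality, severity and expectedness before the event is registered in the CRF". Section 14.4 gives a five-level causality scale.

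Section 14.7 adds a second route for each patient: "At the 30 day visit an assessment will be made where we specifically ask for all SAEs prespecified in this protocol". Section 14.6 lists extremity ischaemia and "Abdominal and/or pelvic ischemia that may/may not require surgical intervention" as expected under both treatments, and thoracic aortic injury as expected with standard ACLS.

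**The concern.** A checklist headed by the cause cannot count the same event in the same way in the two arms. A control has no REBOA equipment, so limb ischaemia or groin bleeding after another arterial procedure does not fit the item. In the REBOA arm the site investigator, who knows the allocation, must attribute the event before ticking it.

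These events can occur in controls. Section 10.2.1 lists arterial catheters among the devices used in both groups, and the shared table in 12.2 records PCI, ECMO and other cardiac interventions for all delivered patients. In the REBOA arm the sheath may be reused for PCI or ECMO (section 9.4), which makes attribution uncertain.

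The protocol gives its own example. Section 13.1.3 reports that one pilot patient had an ischaemic colon and a hemicolectomy, and that an investigation found REBOA not to be the cause. Under this heading such a case would not be ticked, and the list has no visceral item apart from the open one. Whether such harm exceeds its background rate can be judged only by counting it in both arms regardless of attribution. A by-arm safety table that draws on this item could mislead in either direction.

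**Working it through.** The protocol states no complication rate, so there is no figure to reproduce. The main check sets the sections side by side.

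**1. What the item can hold.** The table covers both arms, but the heading admits only events attributed to REBOA equipment. On a literal reading the control count for the seven named items is zero by construction on this checklist. An event whose cause cannot be assessed is classed as possible in section 14.4, and a yes/no field for related events has no place for that class.

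**2. What the other routes recover.**

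| Event type | Other route in both arms | Prompted equally? |
|---|---|---|
| Any event before hospital | Full recording (14.8) | Yes |
| Serious limb or abdominal/pelvic ischaemia | Day-30 question (14.7 with the common list in 14.6) | Yes |
| Serious aortic injury | Day-30 question (14.7 with the ACLS list in 14.6) | Yes |
| Serious access-site event | Day-30 question, but 14.6 lists these events under REBOA only | Unclear |
| Non-serious in-hospital bleeding or infection | Journal or discharge-note review (14.2, 14.8) | No: named prompt only on the REBOA-headed item |

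**3. The recording window.** Section 14.7 ends the standard period for adverse events at hospital admission and takes serious events to day 30. Section 14.2 has the journal of each admitted patient reviewed for adverse events at 30 days. Section 14.8 collects events up to day 30 from the discharge note and a paper CRF. The last row of the table therefore depends on which section governs.

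**4. Illustration of size, on assumed values.** Let p be the same true risk in both arms, a the share of events captured in the REBOA arm over all routes, and c the share captured in controls. The apparent difference, REBOA minus control, is p × (a − c). The true difference is zero.

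| p (assumed) | a = 1, c = 1 | a = 1, c = 0.5 | a = 1, c = 0 | a = 0.5, c = 1 |
|---|---|---|---|---|
| 2% | 0 | +1 point | +2 points | −1 point |
| 5% | 0 | +2.5 points | +5 points | −2.5 points |
| 10% | 0 | +5 points | +10 points | −5 points |

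The column with c = 0 is a limit: no other route would recover any control event. The last column is the opposite error, where half the REBOA-arm events are judged unrelated and lost while all control events are found.

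**5. Counts.** Suppose the number delivered to hospital is close to the number with ROSC at the section 9.2 rates (an assumption). Then 100 × 0.18 = 18 to 100 × 0.36 = 36 patients per arm are at risk. Expected events per arm run from 18 × 0.02 = 0.36 to 36 × 0.10 = 3.6. With so few, one or two missed events would change the picture.

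**The case against.** The strongest reply is that the checklist is an extra device-complication list, which is a legitimate safety tool, and that the adverse event record is kept elsewhere. Sections 14.2, 14.7 and 14.8 apply to both arms and rate causality separately, section 14.9.1 has its own serious event form, and an external panel reviews every randomised patient (13.1.1). Nothing says that the incidence endpoint is computed from the checklist. Most of the seven items would usually be serious and so fall under the day-30 question. Visceral harm is also followed through laboratory values, urine output, renal replacement and radiology in all delivered patients. The CRF schedule and the reportable-events flowchart are figures not shown, so the real field layout is unknown.

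Much of this stands, and it rules out two stronger readings that a reader might infer. One is that these complications are solicited only as REBOA-related. The day-30 question, read with the lists in 14.6, contradicts that for serious limb, abdominal/pelvic and aortic events. The other is that adverse events cannot be compared between arms. Serious events and pre-hospital events are recorded in both, so the comparison is distorted for some event types rather than impossible. The endpoint is exploratory, the objective descriptive, and no between-arm test is stated. A control event that does not fit the checklist can still enter the general record.

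The reply does not remove the unequal prompting. Journal review without a named prompt is not equivalent to a dated yes/no question. If 14.7 governs, non-serious in-hospital events fall outside standard recording in both arms, yet the checklist still collects them for one; bias then arises if the two sources are pooled, which the protocol neither states nor excludes.

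**Conclusion.** The point holds as one of unequal ascertainment. The section 12.2 heading merges occurrence with attribution in a table meant for both arms, at odds with the adverse event definition, the all-events endpoint and the separate causality rating elsewhere in the protocol. The effect is concentrated in non-serious in-hospital access-site haemorrhage and infection, with some doubt over serious access-site events.

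The bias could run against REBOA, through prompting, or in its favour, through events dropped as unrelated. Its size cannot be fixed from the protocol. The illustrative range is from no distortion to 10 points at an assumed 10% risk with no recovery in controls, and nearer zero the better record review works. The conclusion rests on the literal wording of the item, since the CRF itself was not available. The sample size and the primary endpoint are unaffected. The item is still worth changing, because complications not captured prospectively may not be recoverable later.

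**What to change.** - Rename the item neutrally: vascular, limb, visceral-ischaemia, access-site and infection complications.
- Collect the same dated yes/no list for every patient delivered to hospital, in both arms.
- Add the abdominal/pelvic ischaemia item that section 14.6 already names for both treatments.
- Record relatedness in a separate field on the section 14.4 scale.
- Report incidence by arm regardless of relatedness, with related events as a subset.
- Reconcile the adverse event window in 14.7 with 14.2 and 14.8.

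The cost is one relabelled CRF block, opened to controls, and slightly more abstraction per control patient at a chart review that is already planned. Headline complication counts will rise because background events are then counted in both arms; the related-event subset keeps the device signal visible.
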